**Cog impairment** using the **French Telephone Interview for Cognitive Status Modified (F-TICS-m).** The TICS scale is a tool for screening for memory disorders. It evaluates time orientation, spatial orientation, immediate memory, calculation, semantic memory, delayed recall, language, understanding of an instruction. Cut offs of 24 and 34 are used (a score less than 24 corresponds to dementia, a score between 24 and 33 corresponds to mild cognitive impairment and a score more than 34 corresponds to a normal condition). This scale was validated in French by telephone [19].**Depression and anxiety** using the **hospital anxiety and depression scale (HADS)**. The anxiety and depression score through the HADS seeks to identify an anxiety-depressive symptomatology and assess its severity. It is composed of 14 items divided into 2 scores of seven items each: a depression score (one for dysphoria, one for deceleration and five for the anhedonic dimension) and an anxiety score. Each item is rated from 0 to 3, allowing to obtain 2 scores. The maximum score for each score is 21. This scale was validated in French by telephone and in a self-administered collection mode [20].**Fatigue** using the **Fatigue Severity Scale (FSS).** The fatigue score through the FSS measures the impact of fatigue on different functions. This is a short questionnaire of nine questions, to which the patient answers on a scale from 1 to 7. The overall score is the average of all the scores obtained on each of the 9 questions. The higher the result, the greater the fatigue. A threshold of 5.5 is often used to differentiate high and low fatigue. This scale was validated in French in a self-administered collection mode [21].**Genito-sexual disorders** using closed-ended question “yes/no”.**Limitations of activities** using the **modified Rankin Scale (mRS)** [23] and the **Barthel Index (BI)** [22]. The modified Rankin Scale (mRS) and the Barthel Index (BI) are commonly used scales measuring the actual abilities of the stroke patient in the basic activities that determine autonomy. The mRS is a more global scale, which measures functional independence rather than the performance of specific tasks. In this way, mental as well as physical adaptations following neurological deficits are assessed. The scale consists of 7 levels, from 0 to 6, with 0 corresponding to no symptoms and 6 corresponding to death. Cut offs of 2 is used (a score less than or equal to 2 corresponds to independence, a score greater than 2 corresponds to dependence). This scale was validated in French by telephone and in self or hetero-administered data collection mode. The IB was developed in 1965 [22] and later modified by Granger and colleagues [43] to measure patient performance in 10 activities of daily living. The IB is considered a sensitive and reliable disability scale for stroke patients. The IB items can be divided into two groups: one, related to self-care (diet, grooming, bathing, clothing, urinary and anal continence, and toilet use) and the other, related to mobility (ambulation, transfers and stair climbing). The maximum score is 100, which indicates that the patient is totally independent in physical functioning. The lowest score is 0, which represents a totally dependent bedridden state. A dependency to consider a return home is usually defined by a score greater than or equal to 60. The IB is a scale validated in French in a data collection mode by interview (hetero-administered).**Participation restrictions** using the **Community Integration Questionnaire (CIQ)**. The CIQ assesses disability for brainy people in three areas: home integration (active participation in the functioning of the home or household), social integration (participation in social activities outside the home), productivity (regular work performance). It is composed of three sub-scores: home integration [0–12], social integration [0–10], productivity [0–7]. The total CIQ score [0–29] is the sum of the 3 sub-scores.

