### Evaluation criteria

The main evaluation criteria is post-stroke activity limitations by the mRS grouped into three categories ([0; 2]: independence;[3; 5]: dependence; 6: death), at 3 months and 1 year after the acute episode.

The secondary evaluation criteria are:

Other post-stroke sequelae at 3 months and 1 year
◦ Post-stroke cognitive disorders by TICS score grouped into 3 categories (24: dementia; [24; 33]: MCI; 34: normal) at 3 months and 1 year after the acute episode.◦ Post-stroke anxiety and depression disorders by HADS score according to 2 sub-score of anxiety and depression, each grouped into 3 categories ([0; 7]: absence of cases; [8; 10]: questionable state; [11; 21]: certain state) at 3 months and 1 year after the acute episode.◦ Post-stroke fatigue by the FSS score grouped into 2 categories (5.5: low fatigue; 5.5: high fatigue) at 3 months and 1 year after the acute episode.

Post-stroke activity limitations by BI grouped into 4 categories (< 20: bedridden; [20–59]: partial autonomy; [60–79]: autonomy for return home; 80: complete autonomy) at 3 months and 1 year after the acute episode. Restrictions on post-stroke participation by the CIQ-R score grouped into 4 categories ([0–12]: home integration; [0–10]: social integration; [0–7]: productivity; [0–6]: electronic social networking) at 3 months and 1 year after the acute episode. Patient clusters responding to pathways with common or similar characteristics (pathway typology).

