### Data management and statistical analysis

#### Sample size selection

The primary endpoint is the mRS, measured at 3 months and 1 year after the stroke. Based on data from a pilot study, we assume a prevalence of independence of 51%, dependence of 30% and death of 19%. Several simulations were performed by varying the frequency of exposure to the risk factor studied (very rare to very common). By fixing the risk of first species at 5% and the power of the association test at 80%, to show an odds ratio of at least 2 (odds ratios to move to a higher class: independence to dependence or death, dependence on death), 368 patients should be included to cover a change in exposure to the risk factor studied, ranging from 20% (rare exposure) to 80% (frequent exposure).

The study is stratified on the NIHSS score assessed at inclusion (at the end of the hospital stay for acute episode management) in 3 categories (≤6, 7–16, > 16) and needs to include 368 patients per category of NIHSS or 1104 patients in total (software R v3.3.1).

To account for an estimated 5 to 10% of lost to follow-up, it is necessary to include 1210 patients.

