#### Statistical analysis

##### Analysis strategy

The analysis of the assessment criteria will be carried out on available data, i.e. without any replacement of missing data. For the analysis of the primary endpoint, a sensitivity analysis of missing data, using a multiple imputation method, may be considered. The analysis will be carried out using the SAS 9.3 software (or later version) considering a risk of first species fixed at α = 5%. A statistical analysis plan will be defined blind data.

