##### Analysis plan

Characteristics of patients at inclusion and during the study.

Patients will be described to the following variables: compliance with eligibility criteria; socio-demographic, clinical, and pathways characteristics. A description of the violations of the protocol, causes of death and abandonment will be made and patients who have died, lost sight of, or abandoned research may be described and compared with other patients.

Analysis of the primary endpoint.

The mRS, the primary endpoint, is an ordered variable with three response modalities. The analysis is based on a Proportional Odds Model, assuming an identical odds ratio for each possible dichotomization of the criterion.

In order to take into account the correlation between the measurement of the mRS at 3 months and that one at 1 year, a random effect on the time will be systematically added to the models.

The odds proportionality hypothesis and the log-linearity hypothesis will be systematically checked.

Analysis of secondary endpoints
◦ Typology of the different patient stroke pathways

In order to identify the types of paths, a hierarchical clustering, or latent class clustering, will be carried out.
◦ Stroke elements associated with post-stroke sequelae

In order to evaluate the association between the pathway elements and each of the identified sequelae, linear, logistic or polytomic regression models with random effects will be implemented. The assumptions underlying the modelling used will be systematically verified.
◦ Social and geographical inequalities in care

The social and geographical characteristics of the patients included will be described and compared, using the descriptive and comparative statistical methods detailed above, between the different types of pathways identified.

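### Only the mRS has a death category, so the Barthel, cognition, mood, fatigue and participation results rest on survivors, and a pathway component that lowers mortality can appear associated with worse sequelae

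*Protocol article*

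**What the plan says.** All references are to the protocol article.

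- **Primary endpoint (Evaluation criteria).** The mRS has three ordered levels: independence, dependence and "6: death), at 3 months and 1 year after the acute episode".
- **Barthel Index (Evaluation criteria).** "Post-stroke activity limitations by BI grouped into 4 categories (< 20: bedridden", followed by three better categories. The scale description under Data sources makes the floor a living state: "The lowest score is 0, which represents a totally dependent bedridden state".
- **Other scales (Evaluation criteria).** The HADS sub-scores are cut as "0; 7]: absence of cases; [8; 10]: questionable state; [11; 21]: certain state". TICS has three cognitive categories and FSS two fatigue categories. For participation: "Restrictions on post-stroke participation by the CIQ-R score grouped into 4 categories", where the four items listed are sub-score ranges. None of these includes death.
- **Collection (Ad hoc collection of sequelae and elements of pathways).** The scales are obtained by telephone interview or by mailed questionnaire.
- **Analysis set (Analysis strategy).** "The analysis of the assessment criteria will be carried out on available data, i.e. without any replacement of missing data". A multiple-imputation sensitivity analysis is optional and covers the primary endpoint only.
- **Models (Analysis plan).** For the sequelae, "linear, logistic or polytomic regression models with random effects will be implemented". Comparing patients who died with the others is optional.
- **Expected mortality (Sample size selection).** "we assume a prevalence of independence of 51%, dependence of 30% and death of 19" per cent. The time point is not stated.

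**The concern.** The first secondary objective is to find pathway components associated with these sequelae, and the Study design section places the analysis within a causal model. Pathway components may affect survival. If they do, a comparison restricted to patients alive at 3 months or 1 year compares groups selected differently by survival. A component that keeps severely disabled patients alive adds them to the worst categories among the exposed, while their unexposed counterparts have died and have no value. An association with worse sequelae can then arise although no patient was made worse.

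The mRS and the Barthel Index are both presented as measures of activity limitation. They could disagree for the same component only because one counts death and the other does not, and the planned output would give the reader no way to tell this from a real association.

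**Working it through.** **1. The plan's own figure.** Inputs from Sample size selection: distribution 0.51/0.30/0.19, odds ratio 2, alpha 5%, power 80%, exposure e = 20% or 80%. Two-sided alpha is assumed, as the text does not state it. Whitehead's proportional-odds formula:

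N = 3(z_α/2 + z_power)² / [e(1−e)(ln OR)²(1 − Σp³)]

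- Σp³ = 0.1327 + 0.0270 + 0.0069 = 0.1665
- N = 3(1.960 + 0.842)² / [0.16 × 0.4805 × 0.8335] = 367.5, so 368 per stratum and 3 × 368 = 1104

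The planned size reproduces, with death counted as an outcome level.

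**2. How many patients have no value on the secondary scales.** If 19% have died by the time point concerned, 0.19 × 1104 = 210 patients have none. On average 0.81 × 368 = 298 per stratum remain, before loss to follow-up.

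**3. A pure survival benefit, extreme case.** The documents give no Barthel distribution, so mRS dependence stands in for Barthel dependence. Per 100 patients:

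| | Independent | Dependent | Dead |
|---|---|---|---|
| Unexposed (plan's split) | 51 | 30 | 19 |
| Exposed (assumed: 7 deaths prevented, all 7 survive dependent) | 51 | 37 | 12 |

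- Dependent among survivors: 30/81 = 37.0% against 37/88 = 42.0%
- Survivor odds ratio: (37/51)/(30/51) = 1.23
- Dependence-or-death odds ratio: (49/51)/(49/51) = 1.00
- Death odds ratio: (12/88)/(19/81) = 0.58

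If deaths fall from 19 to 16, 9.5 or 5 under the same assumption, the survivor odds ratio is 1.10, 1.32 or 1.47, and the dependence-or-death odds ratio stays at 1.00.

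**4. When does the sign change?** Let s patients per 100 be saved, a share f of them dependent. The survivor odds ratio is 1 when (30 + sf)/(51 + s(1−f)) = 30/51. This gives 51f = 30(1−f), so f = 30/81 = 37.0%, whatever s is. With deaths halved (s = 9.5):

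| Share of saved patients dependent | 0% | 25% | 50% | 75% | 100% |
|---|---|---|---|---|---|
| Survivor odds ratio | 0.84 | 0.95 | 1.06 | 1.18 | 1.32 |

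**5. A direct benefit as well.** With s = 9.5 and f = 100%, suppose m further patients per 100 move from dependence to independence. The odds ratio returns to 1 when (39.5 − m)/(51 + m) = 30/51, so m = 9.5/(1 + 30/51) = 6.0. If instead the component acts at a common odds ratio of 0.5 across the mRS, the exposed split is 67.5/22.0/10.5 and the survivor odds ratio is (22.0/67.5)/(30/51) = 0.55, still protective.

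**6. Dependence on mortality.** Stratum mortality is not given. If it were 5% or 40% (assumed), with the plan's survivor split, deaths halved and all those saved dependent, the survivor odds ratio would be 1.07 or 1.90.

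**The case against.** The case on the other side has several parts.

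- **The primary analysis already counts deaths.** In the extreme case the odds ratios at the two mRS cut points are 1.00 and 0.58. That violates proportional odds, which the Analysis plan says will be checked. This stands for the mRS. Whether the check would have power to detect it is unknown, and it would not change how the Barthel result reads.
- **Survivor framing is partly present.** The Background ties sequelae to patients who survive, the Discussion speaks of a cohort of survivors, and the objectives are worded as associations. This softens the point. It does not remove it, because the causal model invites the stronger interpretation.
- **Strata and adjustment help.** Stratifying on discharge NIHSS and adjusting for known prognostic factors should reduce selection by severity, though they cannot be relied on to eliminate it.
- **An unseen analysis plan may deal with deaths.** It may. But the category lists and the available-data rule are fixed in this document, and following them as written gives survivors-only results.

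A reader might also infer more than the documents support:

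- *That a life-saving component will look harmful.* The sign depends on who is saved and on any direct benefit (working, steps 4 and 5).
- *That a patient who dies drops out altogether.* A patient who dies after 3 months keeps the 3-month values, and every death counts in the mRS.
- *That the distortion is greatest at NIHSS above 16.* This is plausible, but no stratum mortality is given.
- *That the same sizes apply to cognition, mood, fatigue and participation.* No distributions are given for those scales.

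**Conclusion.** The point holds as a possibility that the plan should guard against. As written, the Barthel, TICS, HADS, FSS and CIQ-R results at each time point describe patients alive then, with 19% deaths assumed overall. From the plan's own 51/30/19 split, a pure survival benefit can give a survivor odds ratio for dependence of 1.23 while dependence-or-death is unchanged. This rests on the extreme assumption that every saved patient is dependent and nobody else benefits, and on mRS dependence standing in for Barthel dependence. Below a dependent share of about 37% among those saved, the ratio falls under 1. For the other four scales neither size nor direction can be computed. The primary endpoint is unaffected. This is a worthwhile, inexpensive improvement to a secondary objective.

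**What to change.** 1. **Barthel Index.** In Evaluation criteria and Analysis plan, add an analysis at 3 months and 1 year with death as the worst ordered level, mirroring the mRS. Keep the survivors-only analysis beside it.
2. **TICS, HADS, FSS and CIQ-R.** Keep the planned models. Word the results as associations among survivors, and beside each report the association of the same pathway component with death at the same time point.

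The second step shows the survivor selection but does not remove it. Adding death as an unordered category in a polytomous model would not remove it either: the contrast between living categories would still be (37/51)/(30/51) = 1.23 in the example. Nor would it suit CIQ-R, whose four listed categories are sub-score ranges.

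**Cost.** A change of wording and a little more analysis. No new data are needed, since vital status is already collected (Data sources; Procedure for searching for lost-of-follow-up). The drawback is that the added Barthel analysis is a death-or-disability measure that overlaps the primary endpoint, which is why the survivors-only result should stay beside it.

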### Data sources and data collection

#### Data sources

Three types of data sources are considered (Table 1):

**Table 1 Tab1:** Summary of Stroke Patient Data Collection – PAPASéPA

	Inclusion visit	Follow-up at 3 months post-stroke	Follow-up at 1 year post-stroke
Verification of eligibility criteria	✓		
Patient information^1^ + Oral consent	✓		
Data on the care, socio-demographic and clinical pathways (history, severity, complication during the stay ...) to the acute phase (pre-hospitalization and hospitalization) from the ObA2 Observatory ^2^	✓		
Hospitalization data, consultations, acts, outpatient care from the SNDS^3^	Continuous collection		
Clinical data (ad hoc collection):			
- Severity of stroke: NIHSS at discharge	✓		
- Risk factors (alcohol)	✓		
Stroke pathways data (ad hoc collection)^4^			
- Patient referral ^4^	✓		
- Level of education ^5^	✓		
- Professionnal activity ^5^	✓		
- Marital status ^5^	✓	✓	✓
- Cohabitation status ^5^	✓	✓	✓
- Ability to drive ^5^	✓	✓	✓
- Place of life ^5^	✓	✓	✓
- Participation in a therapeutic education program ^5^		✓	✓
- Medical and social care ^5^		✓	✓
- Allowances for disability ^5^		✓	✓
- Family/Caregiver ^5^		✓	✓
- Development and technique to improve autonomy and home care ^5^		✓	✓
- Technical assistance for walking ^5^		✓	✓
- Legal background ^5^		✓	✓
Sequelae post-stroke (ad hoc collection)			
Cognitive disorders (TICS*) ^5^		✓	✓
Anxiety-depressive disorders (HADS**)(Self-assessment)^6^		✓	✓
Fatigue (FSS***) (Self-assessment)^6^		✓	✓
Activity limitations (BI ǂ) (Self-assessment)^6^	✓	✓	✓
Activity limitations (MRSǁ) ^5^	✓	✓	✓
Participation restriction (CIQ-R§) (Self-assessment) ^6^		✓	✓

*Telephone Interview for Cognitive Status; **hospital anxiety and depression scale; ***Fatigue Severity Scale; ǂBarthel Index; ǁmodified Ranking scale; §Community Questionnaire

^1^ Address; telephone number

^2^ Type of stroke; Severity (NIHSS) at admission; Gender; Age; History of Neuro-cardiovascular; History of neuropsychiatric disorders; Anticoagulant / antiaggregant treatments; Rankin before stroke; Date/time start of symptoms; Date/ time call to general practitioner; Date/time call to emergency medical services; Place of occurrence of the stroke; Mode of transport; Date/time of admission to hospital; Type of hospitalization unit; Performing thrombolysis / tele-thrombolysis / thrombectomy; Type of antithrombotic treatment; Complication during stay; duration of stay

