^3^ Number / type / duration of hospitalization in medicine or surgery, rehabilitation, psychiatry departments. Hospitalization at home; Number / type of medical and paramedical consultations at hospital; Medical ambulatory care: number / type of medical consultations (general practitioner, neurologist, functional rehabilitation physician, cardiologist) and number of care periods, total duration of each care period / type of paramedical consultations (physiotherapy; speech therapy; orthopsy); Quantity of drug deliveries (antiaggregant, antihypertensive, statin or anticoagulant treatment, analgesic), external medical consultations for neurology, rehabilitation, cardiology in health institutions; Vital status of patients

^4^ Patient referral (admission to the hospitalization area of the institution, transfer to another institution), Level of education (INSEE classification); Marital status (Married - Accessed - Partner; Separated - Divorced – Widowed; Single); Cohabitation status (couple; in family- friends; institution), Ability to drive (yes, no); Place of life (home, institution, medico-social structure), Medical-social care (services to support social life, services to help and support at home, services to provide nursing care at home, services to provide medical and social support), Family/Caregiver (yes, no); Development and technique to improve autonomy (yes, no); Legal background (Curatorship, Guardianship)

^5^ Data collected by telephone by the nurse

^6^ Postal delivery to the participant’s home

Extraction of data from two existing databases: the ObA2 cohort and the French National Health Data System (*Système National des Données de Santé* – SNDS). The extractions from existing databases will provide the main information about care pathways, patient characteristics and stroke characteristics.

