◦ Number / type / duration of hospitalization in medicine or surgery departments, rehabilitation department, psychiatry department and hospitalization at home. Hospitalisations will be classified into three categories corresponding to hospital stays with different clinical meanings with regard to the evolution of stroke (readmission for management of stroke recurrence and post-stroke complications, readjustment for post-stroke follow-up and secondary prevention of stroke and re-hospitalizations to manage a clinical situation not related to stroke);◦ Number / type of medical and paramedical consultations at hospital;◦ Medical ambulatory care: number / type of medical consultations (general practitioner, neurologist, functional rehabilitation physician, cardiologist) and of paramedical consultations (physiotherapy, speech therapy, orthopsy), number of care periods, total duration of each care period;◦ Quantity of drug deliveries (antiaggregant, antihypertensive, statin or anticoagulant treatment, analgesic);◦ Vital status of patients.

**Ad hoc collection** at any of three points in the study (initial episode, at 3 months and 1 year after the initial episode).

The collection time for each variable is specified in Table 1. The categories of variables collected are as follows:
◦ **Clinical data:** risk factors (Alcohol), severity of stroke at discharge (NIHSS)◦ **Stroke life pathways data:** patient referral, level of education, marital status, cohabitation status, professional activity, ability to drive, place of life, participation to a therapeutic education program, medical and social care, allowances for disability, presence of family and caregiver, development and technique to improve autonomy and home care, technical assistance for walking, legal background.◦ **Post-stroke sequelae assessment**

A selection of scales measuring each of the dimensions explored in our project was selected, based on elements of feasibility, frequency of use in the exploration of the dimension considered and metrological performance (validity and reproducibility): The mode of collection of sequelae has been adapted according to the validated mode of administration for each of the scales. The following sequelae are assessed:

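### The CIQ-R participation endpoint lists sub-score ranges as if they were categories, and Table 1 contradicts the text on how the Barthel Index is collected

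*Protocol article*

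**What the plan says.** **Participation restriction.** Objectives names this among the sequelae of the first secondary objective. Evaluation criteria defines the endpoint at 3 months and 1 year as "the CIQ-R score grouped into 4 categories ([0–12]: home integration; [0–10]: social integration; [0–7]: productivity; [0–6]: electronic social networking". The instrument description under Data sources has participation measured "using the Community Integration Questionnaire (CIQ", the unrevised instrument. It continues: "It is composed of three sub-scores: home integration [0–12], social integration [0–10], productivity [0–7", and then "The total CIQ score [0–29] is the sum of the 3 sub-scores". Electronic social networking does not appear there. Table 1, the description of the mailing and Evaluation criteria all name the CIQ-R.

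**Barthel Index.** Table 1 lists it as "Activity limitations (BI ǂ) (Self-assessment)^6", ticked at inclusion, 3 months and 1 year. Footnote 6 reads "Postal delivery to the participant’s home". The text under Data sources sets a general rule: "The mode of collection of sequelae has been adapted according to the validated mode of administration for each of the scales". For this scale it adds: "The IB is a scale validated in French in a data collection mode by interview (hetero-administered".

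The section on ad hoc collection of sequelae and elements of pathways puts FSS, HADS and CIQ-R in the mailing. It lists the Barthel Index with F-TICS-m and mRS among the scales administered at follow-up, directly after the telephone step. At discharge it lists the Barthel Index with NIHSS and mRS, at a visit the research nurse makes on site.

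**The concern.** An endpoint described as grouped into categories needs bands that do not overlap and that cover the scale. The four CIQ-R bands all start at zero, and each carries the name of a sub-scale. Read literally, the rule cannot put a patient in a group, and no cut-off for restricted participation is given anywhere in the article. The two descriptions also differ in their number of components, so the instrument to be mailed and scored is not settled.

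For the Barthel Index the question is who fills it in. Table 1 is the collection schedule, and a postal pack could reasonably be assembled from it. A scale that the article says is validated in French by interview would then be gathered by unvalidated postal self-report, or by a caregiver, whom the mailing procedure also allows to complete the forms. That would break the article's own rule on mode of administration.

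**Working it through.** **1. The stated CIQ total.** Sub-score maxima from Data sources: home 12, social 10, productivity 7. Sum: 12 + 10 + 7 = 29. This reproduces the stated total of 0–29 for the three-part version.

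**2. The Evaluation criteria list.** Its first three ranges (0–12, 0–10, 0–7) are identical, with the same labels, to the three sub-score ranges in Data sources. The fourth (0–6, electronic social networking) is new. The list is therefore one of sub-scores. If the four maxima were added, the sum would be 12 + 10 + 7 + 6 = 35. The article states no such total.

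**3. The list read literally, as categories of one score.** For each whole-number score, count the ranges that contain it:

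| Score | Number of ranges containing it |
|---|---|
| 0–6 | 4 |
| 7 | 3 |
| 8–10 | 2 |
| 11–12 | 1 |
| 13 or more | 0 |

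Only two values, 11 and 12, get a unique category. On the stated 0–29 scale, 29 − 13 + 1 = 17 of the 30 possible values get none. The ranges are neither exclusive nor exhaustive.

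**4. Comparison within the same section.** The HADS entry names two sub-scores and gives each three separate bands: 0–7, 8–10 and 11–21. That is a workable form, and the CIQ-R entry has no counterpart to those bands.

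**5. Barthel categories.** The bands are below 20, 20–59, 60–79, and 80. The last is read here as 80 or more, on the assumption that a sign was lost when the text was extracted. Every value from 0 to 100 in steps of 5 then falls in exactly one band, so the endpoint definition is usable.

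**6. Barthel collection mode, side by side.**

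| Place | Mode |
|---|---|
| Table 1 with footnote 6 | Postal self-assessment at all three times |
| Data sources, general rule | Mode follows the validated mode of each scale |
| Data sources, Barthel description | Validated in French by interview |
| Ad hoc collection, inclusion | Administered on site at the end of the stay |
| Ad hoc collection, mailing | Not in the pack |
| Ad hoc collection, follow-up | Administered with F-TICS-m and mRS |

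Table 1 stands alone against the other five. Its footnote also cannot apply to the inclusion visit, which takes place in hospital.

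**The case against.** The best defence on the CIQ-R is that the intended meaning is easy to see. Each range carries its sub-scale name, three match the instrument description exactly, and 'categories' is a slip for sub-scores. Much of that stands: sub-scores can be analysed, and the remedy adopts that reading. It does not excuse the text, because the article fixes a grouping rule that fails and describes two different versions of the instrument. Nor is this detail that an article may leave to the analysis plan, since the article states a rule and states it wrongly.

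On the Barthel Index, the defence is that the procedure section largely settles the mode and the Table 1 entry looks like a misplaced footnote. That is fair, and it limits the point to a contradiction to be removed.

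A reader might infer more, and the documents do not support it:

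- **That both endpoints are unusable.** The Barthel bands classify every score.
- **That a planned polytomous model for the CIQ-R cannot be fitted.** The analysis plan allows linear, logistic or polytomous models with random effects for the sequelae and assigns none of them to this scale.
- **That two total ranges are in use.** Only 0–29 is stated; 35 is a sum made here.
- **That 2 × 1210 = 2420 Barthel readings are affected.** This ignores the assumed 19% mortality and the 5 to 10% loss to follow-up in Sample size selection. It also applies only if the pack follows Table 1 against the described procedure.
- **That change over time would be mixed with change of mode.** Under Table 1 the 3-month and 1-year readings would share one mode, and change from discharge is not a listed endpoint.

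**Conclusion.** The point holds for two secondary endpoints, in limited form.

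- **CIQ-R.** The grouping rule is wrong as written: it gives a unique category to only two score values and none to any score of 13 or more. The article also describes a three-part CIQ in one place and a four-component CIQ-R in another. This follows from the stated ranges alone and needs no outside figure.
- **Barthel Index.** The categories are sound, given the reading of the top band as 80 or more. The defect is the collection mode in Table 1, which conflicts with the article's mode rule, its validation statement and its described procedure. The practical harm depends on staff following the table rather than the text, and the documents give no basis for putting a number on it.

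The mRS primary endpoint and the sample size are unaffected. Correction is worthwhile because one item is an endpoint rule, the other is part of a collection schedule, and both are nearly free to put right.

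**What to change.** **CIQ-R.** Name one version throughout: the instrument description, Table 1, the mailing and the endpoint list. Replace the four categories with the sub-scores of that version, each treated as quantitative in the linear random-effects models that the analysis plan already permits. Add a total only if the scoring of the chosen version supports one; if all four stated components are summed, the maximum would be 35. If a categorical endpoint is wanted, state mutually exclusive cut-offs for each score, as is done for the HADS.

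**Barthel Index.** Reconcile the Table 1 row with the procedure section: administered by the research nurse, on site at inclusion and by telephone at follow-up. Remove the self-assessment label and footnote 6, and confirm that the scale is not in the postal pack. Moving the row to footnote 5 alone would not be enough, because that footnote describes telephone collection and would not fit the in-hospital visit; a short note on the inclusion mode is needed.

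**Cost.** Wording in the endpoint list and the instrument description, one table row with its note, and a check of the mailing. There is no added burden for patients and no change to the sample size or the primary analysis.
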